## Abstract

**Background:**

Osteoarthritis of the first metatarsophalangeal joint (hallux rigidus) leads to pain and poor function and mobility. Arthrodesis is the gold standard treatment for end-stage disease. Total joint arthroplasties have been attempted, but early loosening has been attributed to dorsally directed shear forces on the metatarsal component. Metallic proximal phalangeal hemiarthroplasty theoretically avoids this. Whilst early results are promising, no comparative trials exist comparing this to arthrodesis.

**Methods/Design:**

The primary objectives are to determine the range of outcome scores between the two treatment arms (to inform a power calculation). Outcome measures will include the MOXFQ, AOFAS-Hallux and EuroQol EQ-5D-5 L. Secondary objectives are to determine the accrual rate, dropout rate and trial acceptability to both patients and surgeons. These data will allow the development of a larger trial with longer follow-up.

This is a prospective randomised controlled single-centre study comparing proximal phalanx hemiarthroplasty (AnaToemic, Arthrex Ltd., Sheffield, UK) with arthrodesis (15 patients in each arm). Randomisation will be performed using a 1:1 allocation ratio in blocks of six.

Patients meeting the eligibility criteria will be recruited from three foot and ankle consultant surgeon’s clinics (East Lancashire Hospitals NHS Trust). If agreeable, informed consent will be obtained before patients are randomised.

The outcome measure scores will be completed pre-operatively and repeated at 6 weeks, 3 months and 12 months. A radiological review will be performed at 6 weeks and 12 months to determine rates of loosening (hemiarthroplasty) and union (arthrodesis). Data on length of stay, return to work, complications and re-operation rates will also be collected.

The analysis will compare the change in outcome scores between treatment groups at all follow-up time points. Scores will be compared using a Student *t*-test, adjusting for scores at baseline.

This study will be conducted in accordance with the current revision of the Declaration of Helsinki (1996) and the ICH-GCP Guideline (International Conference on Harmonisation, Good Clinical Practice, E6(R1), 1996). This study has been approved by the sponsor, the Trust Research & Development office. Ethical approval has been received from the National Research Ethics Service (North East: 12/NE/0385 for protocol version 5.3 dated 3 June 2013).

**Trial registration:**

Current Controlled Trials ISRCTN88273654

## Background

First described in 1887, hallux rigidus refers to the symptoms of degenerative arthritis of the first metatarsophalangeal joint (MTPJ) [1]. It is characterised by pain, loss of motion, primarily dorsiflexion and periarticular osteophyte formation. More common in females, hallux rigidus is thought to affect 1 in 45 individuals over the age of 60 years [2]. Trauma is a frequently cited aetiological factor, especially for unilateral hallux rigidus [3]. Generalised osteoarthritis and inflammatory arthropathies, such as rheumatoid arthritis, can also result in hallux rigidus. Irrespective of the causative factors involved, end-stage disease results in articular cartilage loss and loss of joint space. Subsequent pain and loss of motion results in abnormal gait patterns and can interfere with simple daily tasks such as walking and stair climbing [4]. The severity of hallux rigidus can be classified using the system suggested by Coughlin and Shurnas [5]. Early disease, grades 0 to 2, can respond well to non-operative measures such as non-steroidal anti-inflammatory medication and footwear modification. Cheilectomy to remove impinging dorsal osteophytes can also be successful in early cases as the disease initially affects the dorsal portion of the joint. End-stage disease, grade 3 to 4, does not, however, respond as well to such measures and remaining options include joint arthrodesis or arthroplasty [6].

First MTPJ arthrodesis is currently considered to be the gold standard for the treatment of end-stage hallux rigidus, with reported union rates ranging between 90% and 100% [7]. Arthrodesis does, however, predispose the patient to interphalangeal joint osteoarthritis and the loss of dorsiflexion can interfere with activities such as kneeling and squatting, and wearing footwear with raised heels can be problematic [8,9]. Post-operative rehabilitation can also be prolonged and there is up to a 10% risk of non-union, which may require a revision procedure [7]. Thus as an alternative, arthroplasty of the first MTPJ has been attempted.

Silicone implants were initially used following their successful implantation in the hand. Early results were promising with high rates of patient satisfaction [10]. Unfortunately, problems with silicone wear, osteolysis and foreign body reactions limited their longevity [11,12]. Silicone has therefore been suggested to be a material not suitable for first MTPJ replacement due to its poor ability to withstand the forces encountered.

This led to the development of metallic implants in both total toe replacement and hemiarthroplasty designs [13]. Total toe implants have demonstrated good early patient satisfaction [14]. Early loosening, however, was once again a problem [14,15]. This is thought to be due to the large dorsally directed shear forces the metatarsal implant is exposed to during toe-off [16].

Metallic proximal phalangeal hemiarthroplasty (PPH) may therefore avoid both problems related to silicone wear and loosening related to the shear forces exerted on metatarsal head implants. The literature on the results of these implants is, however, sparse and somewhat conflicting. Townley and Taranow [17] published the largest series of 279 PPHs with follow-up ranging from 10 months to 33 years. This retrospective review reported good or excellent results in 95% of subjects. More recently Sorbie and Saunders [18] published their series of 23 patients treated with PPH with follow-up ranging from 34 to 72 months. They report an improvement in AOFAS score from 57 to 88 with no cases of loosening or osteolysis. In contrast Raikin *et al*. [19] found inferior results for PPH compared to arthrodesis. They conducted a retrospective review of 48 feet, 27 with arthrodeses and 21 with PPHs. Of the arthrodesis group, 85% were deemed to have had a good outcome based upon patient-reported satisfaction, versus 60% in the PPH group, with 5 (24%) of the PPH group requiring re-operation due to loosening. They concluded arthrodesis is a more predictable technique for dealing with hallux rigidus.

The literature is therefore divided regarding the efficacy of PPH for the treatment of hallux rigidus. Studies to date have all been retrospective in nature. The only prospective randomised trial so far has compared total joint arthroplasty versus arthrodesis, and concluded outcomes for arthrodesis were better than arthroplasty [20]. A similar prospective randomised study therefore is required to compare outcomes of PPH versus joint arthrodesis accurately. We therefore propose a randomised controlled trial comparing the AnaToemic PPH (Arthrex Ltd., Sheffield, UK) to first MTPJ arthrodesis. This prosthesis shares similar design features to the BioPro First MPJ Hemi Implant (BioPro, Michigan, USA) but has a better cost profile. Early results reported by Kissler and colleagues are promising, with good improvements in pain scores and revision rates comparable to non-union rates observed with arthrodesis [21].

## Methods/Design

This study will run as a prospective single-centre randomised controlled trial with two parallel treatment arms containing 15 participants each and comparing PPH with arthrodesis (the current gold standard for the treatment for hallux rigidus). The primary objective is to determine the range of improvement in outcome scores following these procedures. The secondary objective is to determine the patient recruitment rate, trial dropout rate (including those lost to follow-up) and the acceptability of the trial as a process to surgeons and patients (by way of qualitative interviews). The combination of the primary and secondary objectives will be used in a power calculation and to design a larger, multi-centre randomised, controlled trial with longer follow-up.

### Patient recruitment

Patients will be screened and recruited by three consultant foot and ankle orthopaedic surgeons from outpatient clinics (in the East Lancashire Hospitals NHS Trust) after confirmation of diagnosis and eligibility (see Table 1). Screening will continue until the target sample size is reached (15 patients in each arm). The number of patients to be recruited has been based on discussions with the trial statistician. There is no published data using the MOXFQ tool to assess differences between PPH and arthrodesis. Therefore, a power calculation was not performed.

**Table 1 T1:** Eligibility criteria

**Inclusion**	**Exclusion**
1. Coughlin grade 3 to 4 hallux rigidus with near constant pain and stiffness at least at extremes of passive motion +/− mid range of motion pain, where conservative treatment measures have failed	Inflammatory arthritis
	Active infection
	Severe vascular or neurological deficit affecting the lower limbs
	Hallux valgus angle >15°
	Inadequate or poor quality bone stock
2. Aged 45 years or above	Any previous surgery to the first MTPJ other than a cheilectomy
3. Male or female	
4. Able to give informed consent	
	Significant and symptomatic interphalangeal joint or sesamoid-metatarsal osteoarthritis

Patients who meet the eligibility criteria will be provided with a patient information sheet and given 1 to 2 weeks to go over this information. If agreeable, informed consent for entry into the trial will be obtained from patients before randomisation is performed. Randomisation will be performed using a random computer generated sequence with a 1:1 allocation ratio in blocks of six. The online website Sealed Envelope [22] has been used to do this. Allocation concealment will be ensured by using a locked spreadsheet, which will only reveal the allocated treatment arm after a patient’s hospital number and study number have been entered. Given the nature of surgical procedures, the only person involved in this trial who will remain blinded to treatment arm allocation is the statistician. Surgeons and patients cannot be blinded to the treatment arm. The outcome measures used in this study are all patient administered and therefore this study does not require a blinded assessor.

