### Trial status

The trial is currently recruiting participants.

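### A single published block size of six, at one unblinded centre where the recruiting surgeons also operate, lets up to an expected quarter of allocations be deduced just before randomisation

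*Protocol article*

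**What the plan says.** The Patient recruitment section states: "Randomisation will be performed using a random computer generated sequence with a 1:1 allocation ratio in blocks of six". The abstract (Methods/Design) repeats it: "Randomisation will be performed using a 1:1 allocation ratio in blocks of six". Neither place mentions a second size, random variation of size or stratification.

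The setting is given elsewhere in the article:

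- **Centre and size.** "This study will run as a prospective single-centre randomised controlled trial with two parallel treatment arms containing 15 participants each" (Methods/Design).
- **Who recruits.** "Patients will be screened and recruited by three consultant foot and ankle orthopaedic surgeons from outpatient clinics" (Patient recruitment). Under Interventions, one of the same three consultants performs each operation.
- **Blinding.** "Surgeons and patients cannot be blinded to the treatment arm" (Patient recruitment). The statistician is the only person kept blind.
- **Concealment.** A locked spreadsheet shows the arm only once the patient's hospital and study numbers are entered. Consent comes before randomisation, after 1 to 2 weeks with the information sheet. Table 2 places screening at week 0 and both consent and randomisation at week 2.
- **Timing of publication.** "The trial is currently recruiting participants" (Trial status).

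**The concern.** In a 1:1 block of six, once one arm has used its three places the rest of the block is fixed. Someone who knows the block size and the earlier allocations in the block can then name the next arm before it is revealed. Here the size is in print while patients are still being recruited, and the recruiters belong to the small team that carries out the allocated operations.

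A locked spreadsheet prevents anyone reading ahead. It does not prevent counting. Consent before randomisation does not close the gap either, because a recruiter who has deduced the next arm can act earlier, in choosing when to approach a patient or complete consent. Some exclusion criteria in Table 1, such as poor bone stock, also leave room for judgement.

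If that happened, the arms could differ in ways that adjustment for the baseline score would not remove. Statistical methods says the observed effect size will feed the power calculation for the definitive trial, so a bias would carry forward. Recruitment rate is a stated secondary objective and would be affected directly by deferred approaches.

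**Working it through.** The article gives no predictability figure to reproduce, and the sample size has no power inputs ("Therefore, a power calculation was not performed"). The one consistency check available is 30 / 6 = 5 complete blocks, which gives exactly 15 per arm.

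**Inputs.** Block size 6 and ratio 1:1 (Patient recruitment); 30 patients at one centre (Methods/Design). One unstratified sequence is assumed, because no stratification is stated.

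**1. Full knowledge of earlier allocations, immediately before randomisation.** There are C(6,3) = 20 equally likely blocks. A place is certain when one arm already has three.

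- Place 4: the first three are alike in 2 of 20 blocks, 0.1.
- Place 5: the last two are alike in 8 of 20 blocks, 0.4.
- Place 6: always certain, 1.0.

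The sum is 0.1 + 0.4 + 1.0 = 1.5 of 6 = 25%. The closed form for a block of 2m agrees: 2m/(m + 1) = 6/4 = 1.5. Over five blocks, 5 × 1.5 = 7.5 of 30.

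**2. Each surgeon knows only their own patients.** With k equally active surgeons, all three patients who filled the exhausted arm must belong to the surgeon now recruiting, which has probability (1/k)³. The certain share is 0.25/k³:

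- k = 3: 0.25/27 = 0.9%.
- k = 2: 0.25/8 = 3.1%.

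Two is included because Data collection describes the operating surgeons as both senior authors, whereas Patient recruitment and Interventions name three.

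**3. Certainty at first approach, with full sharing.** If one other patient is randomised between approach and randomisation, place 6 must be known after four allocations (0.4) and place 5 after three (0.1): 0.5/6 = 8.3%. If two intervene, only place 6 known after three remains: 0.1/6 = 1.7%. The article gives no accrual rate from which to choose between these.

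**4. Best guess.** Guessing the arm that is behind, and tossing a coin when level, is right with probability 0.5, 0.6, 0.6, 0.7, 0.7 and 1.0 at places 1 to 6. The sum is 4.1, and 4.1/6 = 68.3%.

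**5. Varied block sizes.** A simulation of 20,000 fresh lists of 30 used an observer who sees every allocation and knows the set of sizes but not their order.

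| Sizes | Certain | Best guess correct |
|---|---|---|
| 6 only | 25.0% | 68.3% |
| 4, 6 | 5.7% | 68.8% |
| 2, 4, 6 | 3.8% | 69.9% |
| 4, 6, 8 | 2.3% | 67.5% |

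For 4, 6, 8 this is about 0.7 of 30 certain. A separate simulation of these sizes gave a mean absolute difference between arms of 0.57 patients and a maximum of 4 (13/17).

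**The case against.** Permuted blocks of fixed size are an ordinary choice. The article pairs them with consent before randomisation and a locked spreadsheet, and this is a 30-patient study meant to inform a larger one. Nothing in it is contradictory.

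A reader might infer that a quarter of allocations are known before the patient is approached. The documents do not support that. The 25% applies at the moment of randomisation; Table 2 puts two weeks between screening and randomisation, and three clinics feed one sequence, so other patients may be allocated in between.

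A reader might also infer that, because the surgeons operate, each knows all past allocations. That does not follow. Each operation is done by one of three surgeons, and the article does not say what they see of each other's allocations, or who runs the spreadsheet. Nor does anything suggest that deduction has been used to steer patients.

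A further inference might be that the study's refusal figures would be distorted. Refusals are not among its stated objectives; recruitment rate, dropout and acceptability are.

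The remedy is limited too. It leaves the best-guess rate almost unchanged and helps only patients not yet randomised, whose number is not given.

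These points limit the size of the concern. They do not remove it. Full sharing is plausible in one small team, nothing described prevents it, and Table 2 puts consent in the same study period as randomisation, so the just-before-randomisation figure bears on the timing of consent.

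**Conclusion.** The point stands as a cheap improvement to a design choice, not as an error or a sign of misuse. With one disclosed block size of six, an expected 25% of allocations (7.5 of 30) are certain immediately before randomisation if recruiters know every earlier allocation in the block. This is an upper figure. It falls to about 1% to 3% if surgeons know only their own patients, and at first approach to 8.3% or 1.7% with one or two intervening randomisations. It rests on a single unstratified sequence and on recruiters knowing where each block begins. Any effect on the effect estimate or the recruitment rate is possible, but its size cannot be estimated from the article.

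**What to change.** Complete the current block of six. Then allocate the remaining patients from a regenerated list of randomly ordered blocks of varying size, for example 4, 6 and 8. Withhold the sizes from recruiters and do not publish them until recruitment ends.

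**Gain.** Certain allocations fall to about 2% of those remaining, on the simulation of a fresh list of 30. The best-guess rate stays near 67%, so the change removes certainty and little else. The last place of the block being completed remains deducible.

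**Cost.** A new list, a minor amendment and possibly a small imbalance such as 14/16. That must be reconciled with the stated rule: "Screening will continue until the target sample size is reached (15 patients in each arm". There are two ways:

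- Restate the target as about 15 per arm, 30 in total. No power calculation depends on exact equality, and the 2% figure refers to this option, with the list cut off at the total.
- Choose block sizes that sum to the remaining number. This keeps 15/15, but anyone who knows the total can again deduce at least the final allocation, so certainty would exceed 2%. If only six patients remain, the only choice from 4, 6 and 8 is one block of six, and nothing is gained.

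The first option serves the purpose better.

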### Interventions

Surgery will be performed by one of the three consultant orthopaedic foot and ankle surgeons who are FRCS (Trauma & Orthopaedics) qualified and on the General Medical Council’s Specialist Register.

#### Arthrodesis arm

The procedure will be carried out under either general or regional anaesthesia as directed by the anaesthetist and patient. A local anaesthetic ankle block to the tibial, saphenous, deep and superficial peroneal nerves will be administered prior to the start of the procedure using 20 ml 0.5% bupivicaine. The first MTPJ will be exposed through a longitudinal dorsal or medial skin and capsular incision and the joint surfaces will be prepared, arthrodesed in 10° of dorsiflexion and held with two crossed headless compression screws. Post-operatively the patients will be mobilised in a wedge shoe for 6 weeks.

#### Hemiarthroplasty arm

The hemiarthroplasty device used will be the AnaToemic PPH (Arthrex Ltd., Sheffield, UK) The same surgical approach as used for the arthrodesis group will be employed. Adhesions between the sesamoids and the metatarsal head will be released and osteophytes excised. The component will be inserted uncemented as per the manufacturer’s guidelines, including carrying out a cheilectomy if required to ensure a minimum arc of motion of 80° is achieved. Active and passive mobilisation will be commenced on the second day post-operatively, and a wedge shoe will be worn for 6 weeks. Following this period, these patients will have physiotherapy aimed at increasing the range of motion of the joint.

### Data collection

The primary outcome measure, the MOXFQ, was chosen as it is a validated, patient-reported, foot and ankle questionnaire. It comprises 16 questions and is represented by three domains (walking/standing, pain and social interaction). The MOXFQ has been shown to be reliable, valid, responsive and acceptable in validation studies [23,24].

The AOFAS-Hallux score comprises three areas: pain, function and alignment. This is a clinician-administered questionnaire, scored out of 100. The question relating to MTPJ range of motion will be removed for all patients in both treatment arms post-operatively. This is because the arthrodesis treatment arm will automatically score 0 for this (an arthrodesis by definition is a fused joint). Therefore, post-operative AOFAS-Hallux scores will be scored out of 90. The AOFAS score is very popular for reporting foot and ankle outcomes. However, it does not have extensive or rigorous supporting validation studies. Baumhauer *et al*. [25] raised concerns regarding this score’s reliability and validity in the activity subscale. Ibrahim *et al*. [26] reported satisfactory reliability and responsiveness with acceptable validity at best. For this reason, we have opted to use the MOXFQ score as a primary outcome measure.

The EuroQol EQ-5D-5 L is a standardised measure of health status [27]. It comprises five dimensions (anxiety/depression, mobility, self-care, usual activities and pain/discomfort) and each dimension has five levels of patient-reported severity. When referenced to population-standardised datasets, this provides a health status index value. A visual analogue score for perceived health state makes up the second part of the EQ-5D-5 L.

Trial data will be collected using a structured data collection form, which will include basic patient demographic details and all relevant study questionnaires. These will be completed in paper format. All patient trial paperwork will be stored in individual files in a secure, locked cabinet in the Research & Development main office. Data fields will be checked for completeness and entered into a secure password-protected spreadsheet. This will be stored on a Trust approved, encrypted USB stick and kept locked along with the Trial Site File and patient trial folders.

For all patients, basic demographic data will be recorded following trial consent and randomisation. Outcome scores (MOXFQ, AOFAS and EQ-5D-5 L) will be completed preoperatively and then post-operatively (see Table 2). Details regarding length of hospital stay, return to work, complications and any episodes of repeat surgery will also be collected.

**Table 2 T2:** Schedule of screening, enrolment, randomisation, intervention and assessment

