### Statistical methods

The primary analysis will compare MOXFQ scores between the two treatment groups at 12 months using a *t*-test, adjusting for the score at baseline. A similar analysis will be carried out to investigate differences in secondary outcomes (AOFAS-Hallux and EQ-5D-5 L) between the two treatment groups. Effect sizes will be presented as a point estimate, 95% confidence intervals and *P* values. Rates of patient dropout will be reported at each time point. The observed effect size will be used in a power calculation for a future definitive trial.

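### The AOFAS-Hallux drops its motion item only after surgery, so within-arm improvement is lowered by each patient's baseline motion score (0 to 10 points)

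*Protocol article*

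**What the plan says.** In the protocol article, Data collection describes the AOFAS-Hallux thus: "This is a clinician-administered questionnaire, scored out of 100". It then sets a scoring rule: "The question relating to MTPJ range of motion will be removed for all patients in both treatment arms post-operatively". The reason given is that a fused joint would necessarily score 0 on that question. The consequence is stated as "Therefore, post-operative AOFAS-Hallux scores will be scored out of 90".

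The score is collected before surgery and at 6 weeks, 3 months and 12 months. Three places use the pre-operative value:

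- Methods/Design: "The primary objective is to determine the range of improvement in outcome scores following these procedures".
- Abstract, Methods/Design: "The analysis will compare the change in outcome scores between treatment groups at all follow-up time points". The next sentence there adds adjustment for baseline.
- Statistical methods, after the baseline-adjusted MOXFQ comparison at 12 months: "A similar analysis will be carried out to investigate differences in secondary outcomes (AOFAS-Hallux and EQ-5D-5 L) between the two treatment groups".

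**The concern.** The removal applies to post-operative scores only. As written, the baseline total still contains the motion question, while every follow-up total lacks it. A change score then subtracts a total on one scale from a total on another. A patient who had some motion credit before surgery and is otherwise unchanged would appear to have got worse.

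This pilot exists to supply figures for planning a larger trial, and improvement in outcome scores is its stated primary objective. AOFAS-Hallux is one of the listed measures. If its improvement and the spread of that improvement are computed across mismatched scales, the later trial inherits figures that do not mean what they seem to mean.

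This is not a detail left to a document that is not shown. The article states the rule explicitly and limits it to the post-operative period.

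**Working it through.** **Inputs from the protocol article.** Full scale 100; post-operative scale 90; motion item removed post-operatively in both arms (Data collection). 15 patients per arm (Methods/Design).

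**Size of the removed item.** 100 − 90 = 10 points, which agrees with the article's own figure of 90.

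**Effect on one patient.** Let C0 and C1 be the pre- and post-operative totals on the common items (0 to 90), and m the pre-operative motion score (0 to 10).

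- Planned change = C1 − (C0 + m)
- Like-for-like change = C1 − C0
- Planned minus like-for-like = −m

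So m = 0 gives no shift, m = 5 gives −5 and m = 10 gives −10. A patient at the maximum on both occasions shows 90 − 100 = −10 with no deterioration.

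**Does the removal achieve its purpose?** Suppose the item had been kept and everyone scored 0 on it after surgery. The change would be (C1 + 0) − (C0 + m), which is identical to the planned change. For change scores, then, the rule leaves the automatic zero in place for the arthrodesis arm and extends it to the hemiarthroplasty arm.

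**Effect on the comparison between arms.** The baseline is measured before surgery and allocation is random, so m has the same expectation in both arms and cancels from the expected difference. What remains is precision.

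A simulation illustrates this (20,000 runs, 15 per arm). All its inputs are assumptions, not figures from the article:

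- common-item baseline: mean 50, SD 12
- follow-up: mean 75 at the mean baseline, slope 0.5 on baseline, residual SD 10
- motion item: 0, 5 or 10 with probabilities 0.4, 0.4 and 0.2
- true difference between arms: 5

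| Quantity | As planned (100 then 90) | Same items (90 and 90) |
|---|---|---|
| Mean improvement within one arm | 21.0 | 25.0 |
| Between-arm difference, unadjusted change (SE) | 4.98 (4.47) | 4.97 (4.24) |
| Between-arm difference, baseline-adjusted (SE) | 5.00 (3.78) | 4.99 (3.71) |

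The shortfall within the arm is 25.0 − 21.0 = 4.0. That is simply the assumed mean motion score: 0.4×0 + 0.4×5 + 0.2×10 = 4.0.

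The SE rises by 4.47/4.24 − 1 = 5% without adjustment and by 3.78/3.71 − 1 = 2% with it.

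**Check on the unadjusted SE.** The assumed item has variance 0.4×25 + 0.2×100 − 4² = 14. Like-for-like change has variance (0.5×12)² + 10² = 136. Then √(136×2/15) = 4.26 and √(150×2/15) = 4.47, in line with the simulation.

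**The case against.** The strongest reply is that little depends on this. The MOXFQ is the primary outcome and its analysis is untouched. Data collection itself ranks the AOFAS below the MOXFQ because its validation is weaker. Both the Abstract and Statistical methods adjust for baseline. With baseline as a linear covariate, analysing change or follow-up score gives the same treatment estimate. The effect size that Statistical methods carries into a future power calculation is a between-group quantity, which this scoring does not bias. All of this stands, and it sets the severity.

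A second reply concerns the word understated. On the full 100-point scale a fused joint scores 0 for motion after surgery, so an arthrodesis patient's planned change equals the full-scale change. This also stands: the shortfall is relative to the common 90-point items. A reader might infer that improvement in both arms is biased downward against published results, but for arthrodesis the article's own reasoning contradicts that.

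Three further readings are tempting and go too far:

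- *Every patient's change is too low.* A patient scoring 0 on motion before surgery is unaffected.
- *The error is about a third of the effect.* The ratio would be 10/31 = 32%, using the 57-to-88 improvement cited in Background. It is a ceiling that needs full motion credit before surgery. That is unlikely given entry criteria of grade 3 to 4 disease with stiffness, and the 31 points come from a separate hemiarthroplasty series.
- *Chance imbalance adds 1.1 to 1.5 points of standard error.* With an assumed item SD of 3 to 4, SD×√(2/15) is indeed 1.10 to 1.46. But it applies only to unadjusted change, and independent components combine in quadrature. In the illustration the SE rose by 0.23 unadjusted and by 0.07 adjusted.

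None of these replies removes the mismatch in the within-arm figures.

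**Conclusion.** The point holds in a limited form. Following the scoring rule as written, within-arm AOFAS-Hallux change equals like-for-like change minus the pre-operative motion score. The shift is 0 to 10 points per patient. Its average is unknown, and the 4.0 in the illustration only returns an assumption. It affects the AOFAS part of the improvement named in the primary objective, and the spread of change scores. For change scores, it also defeats the reason given for removing the item.

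It does not bias the comparison between arms, and after baseline adjustment the loss of precision is small. It does not touch the MOXFQ. The conclusion assumes that the pre-operative score is the full 100-point total, as the text implies. If the full protocol also drops the item at baseline, only the article's wording needs correcting.

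Severity: should be fixed, for a secondary outcome.

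**What to change.** Use the same items at every visit for all change and baseline-adjusted AOFAS-Hallux analyses. A sentence such as this would do: *For these analyses the AOFAS-Hallux total excludes the MTPJ motion item at every visit, the pre-operative one included, and runs from 0 to 90.* Report the pre-operative motion item and the 100-point baseline separately, as descriptive data.

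The cost is one scoring sentence. No new data are needed, provided item responses are kept on the completed questionnaires, and it can be settled before analysis.

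There is one small drawback: 90-point changes are not directly comparable with published 100-point changes. For arthrodesis, the full-scale change can be recovered by subtracting the reported motion item (C1 − C0 − m). For hemiarthroplasty it cannot be recovered under either rule, because post-operative motion is not scored.
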